### Screening, enrolment and retention

Patients aged between 10 and 30 years that are admitted to one of the three study wards of the HTD, HCMC, Vietnam, with clinical suspicion of dengue and less than 72 hours of fever are invited to participate in the trial. After giving consent, patients are screened for their eligibility to commence treatment with the trial drug by the study physicians. Blood samples are collected to test for NS1, and AST, ALT and creatinine levels and in female patients, a urine sample is collected for a pregnancy test. Glucose and lactate levels are measured using point-of-care (POC) tests.

All patients will be asked to come back for a final FU visit at 28 days after the onset of fever. Patients will be contacted 3–5 days prior to the FU visit to arrange an appropriate appointment date and time. Any case who misses the FU visit will be contacted by phone either to reschedule the visit or to collect information if patients could not arrange their time to come back. If the patients stay in the hospital for longer than 5 days, due to AEs or any other reason, the treatment for these cases will be at discretion of the attending physicians. No further blood samples or study procedures will be performed from this point onward. However, the final outcome at discharge will be collected in the case report form (CRF;
*Extended data*
^46^).

At discharge, the participants will be offered a referral to nutrition specialists for a consultation of overweight/obesity management. Patients will also be provided with leaflets on healthy eating and lifestyle behaviours.

While not an RCT, this trial is designed to enroll patients contemporaneously with an observational obesity trial, where patients received standard care, to minimize systematic differences between the intervention (metformin) and control group, i.e. patients have the same inclusion /exclusion criteria, enrolled on same wards, with the same standard of care during the same dengue season (to avoid the issue of viral serotype shifts). 

To minimize selection bias, we have set up a system on the dengue wards, to ensure eligible patients are recruited into both studies in a systematic way. This involves only one study enrolling for a 2-week time block. During that time, if a patient fails screening assessment or declines enrollment into one of the trials, they are not eligible for the other.

In addition, we will ensure the predefined inclusion/exclusion criteria for all patients enrolled are strictly adhered to reduce investigator subjective assessment and will carefully document screen failures and all exclusions and withdrawals in the trial. And lastly, we plan to have an intention-to-treat analysis where independent study investigators will perform a blinded outcome assessment for all patients.

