### Secondary endpoints

The secondary endpoints are: fever clearance time (the time from enrolment to sustained body temperature <37.5°C for 48 hours); platelet nadir and highest AST/ALT between days 3 and 8 of illness; percentage increase in haematocrit (HCT) from baseline (using HCT obtained at the 28 day FU visit to reflect baseline); plasma viraemia (area under the log
_10_-transformed viraemia curve from study days 3 to 6); time from enrolment to first undetectable viraemia and first negative NS1 measurement; trend over time (5 days) in VCAM1, CRP, leptin, adiponectin, low density lipoprotein (LDL), and AMPK phosphorylation; and magnitude of activated/proliferating T and NK cells as well as frequency and phenotype of dengue-specific CD4+ and CD8+ T cells, quantified by flow cytometry at enrolment and hospital discharge.

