### Data collection

***Clinical evaluation.*** Patients will be reviewed daily until discharge. All clinical symptoms and signs will be recorded in the CRF. An ultrasound scan will be performed on day 5–6 of illness to detect evidence of fluid accumulation. General management decisions will be at the discretion of the attending ward doctors. Details of all AEs and SAEs will be recorded on specific forms, together with an assessment as to whether the events are likely to have been related to any treatment received. All SAEs will be reported promptly to the DMC and ECs according to policy.

***Laboratory evaluation.*** Full blood count (FBC) and POC glucose and lactate tests will be undertaken daily until discharge. An additional POC glucose test will be performed before their evening meal.

In addition, levels of serum albumin, transaminases (ALT/AST), creatinine, total cholesterol, HDL-cholesterol, LDL-cholesterol, triglycerides, and C-reactive protein (CRP) will be measured on alternate days. All tests will be done more frequently when clinically indicated.

Research samples collected daily until discharge will be used for dengue diagnostics (NS1 antigen detection and PCR assays). Residual blood from FBC samples will be collected for daily plasma viraemia levels. Serology tests (Capture IgM/IgG ELISAs) will be performed on enrolment (acute) and discharge/FU (convalescent) samples. Other laboratory investigations will include endothelial, inflammatory and lipid biomarkers (VCAM1, syndecan-1, leptin, adiponectin), using commercially available ELISAs and Luminex kits, immunological tests (T cell phenotype and functional analysis), and immunometabolism (AMPK phosphorylation). RNA will be extracted from a blood sample collected on study day 2, and will be sequenced to investigate gene expression in the metformin treatment group in comparison to the non-treatment group.

At day 28 of illness, final routine (FBC, biochemistry) and research blood samples will be taken to check whether patients have fully recovered from the acute dengue episode.

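### Ending all sampling once a stay exceeds 5 days removes the discharge immunology sample and the late virology that the secondary endpoints need

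*Protocol article*

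**What the plan says.** All places are in the Protocol article.

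- **Screening, enrolment and retention.** The trigger is "If the patients stay in the hospital for longer than 5 days, due to AEs or any other reason". From then on treatment is left to the attending physicians, and "No further blood samples or study procedures will be performed from this point onward". The one item still collected is the final outcome at discharge. The section does not say whether the 5 days run from admission or from enrolment.
- **Data collection, Laboratory evaluation.** "Full blood count (FBC) and POC glucose and lactate tests will be undertaken daily until discharge". Research samples for NS1 and PCR follow the same daily schedule, and viraemia is measured on blood left over from the blood-count samples. Transaminases belong to a list of tests that ends "C-reactive protein (CRP) will be measured on alternate days". None of these schedules has a 5-day limit.
- **Secondary endpoints.** T and NK cells and dengue-specific T cells are "quantified by flow cytometry at enrolment and hospital discharge". Virology includes the area under the log10 "viraemia curve from study days 3 to 6" and the "time from enrolment to first undetectable viraemia and first negative NS1 measurement". Platelet nadir and highest AST/ALT are taken over illness days 3 to 8.
- **Statistical analysis.** The two clearance times are compared by Cox regression.

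**The concern.** The stop applies to a group selected by its course of illness: patients not yet fit to leave, expressly including those held back by adverse events. If staff follow it, planned endpoint data are missing in those patients and present in patients who go home sooner. An analysis of the available discharge T/NK samples would then describe mainly the shorter stays. An analysis plan cannot repair this, because the samples were never drawn.

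These endpoints feed a decision. The Discussion says that, once safety is established, improvement in any secondary endpoint would justify a larger randomised trial. The comparison is already non-randomised, so a second source of selection is unwelcome. How the control cohort is sampled after day 5 is not described in this article. If controls are sampled to discharge, the observation windows would also differ between groups. That is a possibility to check and not an established fault.

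**Working it through.** The plan gives no figure on this point to reproduce. Its only sizing figure, 80% power for a slope difference of 0.023, concerns the five-day VCAM trend, which the stop does not touch. The check is which endpoint samples fall after the stop.

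**Step 1: the two schedules.** A patient still in hospital after the stop is due a daily blood count and research sample under Data collection, and no sample under Screening, enrolment and retention. Treating the second as a specific exception resolves that pair of rules. Steps 2 to 5 ask whether the exception fits the endpoints.

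**Step 2: T/NK cells.** There are two planned time points, enrolment and discharge. Discharge comes after the stop for every affected patient, so 1 of 2 is lost however the days are counted. Convalescent serology may use the follow-up visit instead; this endpoint has no such alternative.

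**Step 3: clearance times.** Neither definition has an upper day. A patient still viraemic or NS1-positive at the stop is censored there, although still in hospital and available for sampling.

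**Step 4: viraemia area.** Study days 3, 4, 5 and 6 give 4 daily points. A stop after study day 5 loses day 6, so 1 of 4. A stop after study day 6 loses 0 of 4.

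**Step 5: platelets and AST/ALT, illness days 3 to 8.** Assumptions, none fixed by the document:
- enrolment is study day 1, on illness day e = 1, 2, 3 or 4 (entry requires admission within 72 hours of fever onset; day 4 is reached if the onset day counts as day 1);
- alternate-day AST/ALT falls on study days 1, 3, 5 and 7;
- the patient is still in hospital through illness day 8.

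With a stop after study day s, the last sampled illness day is L = e + s − 1, and the platelet days lost are max(0, 8 − L). AST/ALT falls on illness days e, e+2, e+4 and e+6.

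| e | AST/ALT days in window | L (s = 5) | Platelet days lost | AST/ALT lost | L (s = 6) | Platelet days lost | AST/ALT lost |
|---|---|---|---|---|---|---|---|
| 1 | 3, 5, 7 | 5 | 3 | 1 of 3 | 6 | 2 | 1 of 3 |
| 2 | 4, 6, 8 | 6 | 2 | 1 of 3 | 7 | 1 | 1 of 3 |
| 3 | 3, 5, 7 | 7 | 1 | 0 of 3 | 8 | 0 | 0 of 3 |
| 4 | 4, 6, 8 | 8 | 0 | 0 of 3 | 9 | 0 | 0 of 3 |

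If enrolment is instead labelled study day 0 and the stop follows study day 5, then L = e + 5. The platelet losses are those of the s = 6 columns (2, 1, 0, 0), but study day 6 of the viraemia curve is still lost.

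The platelet and AST/ALT counts are maxima. A patient discharged at the stop has the same uncovered days through ordinary discharge, so only days actually spent in hospital after the stop are due to the rule.

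**Not affected:** the five-day adverse event count (primary endpoint), the first data monitoring review and the five-day biomarker trends. Follow-up of adverse events leading to discontinuation also continues. Read literally, the stop would bar the day-28 bloods too, but the same section asks all patients back for that visit, so this is unlikely to be meant.

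**The case against.** The best defence is that the specific rule governs the general one: the drug course ends after 5 days, care returns to the ward, and the trial stops adding procedures. On that reading the sampling schedules do not contradict each other. This is reasonable for the schedules, but it leaves the discharge T/NK endpoint without its sample, so it does not dispose of the point.

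Further objections, and what stands of each:

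- **Cox censoring.** A stop at a fixed day is administrative censoring, which costs information and is not in itself a bias. Sampling until discharge is arguably more outcome-dependent, since discharge follows recovery. The first part stands: for clearance times the harm is lost information. The second is weaker, because patients who leave before the stop are censored at discharge under either rule. Data collected later can also be cut at a common day in the analysis, whereas data never collected cannot be restored.
- **Study day 6.** A viraemia window ending on study day 6 suggests that sampling through that day was intended. This may be so, which is why both counts are shown.
- **Ward tests.** Patients kept in for adverse events will often have platelets and transaminases measured on clinical grounds, so those losses may be smaller than the table shows. This stands. T/NK cells and virology are research samples and gain nothing from it.
- **Control cohort.** Its later sampling belongs to a separate study and need not appear in this article. This stands; the conclusion does not depend on it.
- **Scale.** The study is exploratory, its primary endpoint is untouched, and few patients may stay past the stop. This limits the severity of the point but does not reconcile the stop with the endpoints.

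**Conclusion.** The concern holds and should be fixed; it does not threaten the primary safety comparison. One part rests on no assumption: every patient who stays past the stop loses the discharge T/NK sample, and late viraemia and NS1 clearance go unobserved in the same patients. The missing T/NK data are tied to the course of illness and so are likely to be informative. The study-day-6 viraemia point and the late platelet and AST/ALT values depend on the unstated day count, on the day of enrolment and, for the last two, on what the ward tests. The total effect cannot be computed, because the document gives no length of stay.

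**What to change.** Amend the sentence in Screening, enrolment and retention so that after day 5 only treatment decisions pass to the attending physicians, while the Data collection schedule continues until discharge. This keeps the discharge T/NK sample, viraemia at least to study day 6, NS1, and platelets and AST/ALT to illness day 8 while the patient is in hospital. State the day from which the 5 days are counted and whether enrolment is study day 0 or 1.

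Confirm how long the control cohort is sampled. If its window differs, align it, or restrict between-group comparisons to the window both groups share.

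For treated patients the cost is one sentence and a few more samples from people already in hospital, all of which Data collection already plans. Aligning the controls may need a change in the separate observational study. If that is not possible, restricting to the shared window leaves some late data unused.

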**Figure 1. f1:**
[figure not shown]
Trial flow chart.

The 60 patients receiving treatment will be compared to 60 overweight or obese patients with standard of care (without treatment) recruited contemporaneously from the same wards, with the same enrolment criteria, in an ongoing observational study as the control arm.

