### Statistical considerations

***Sample size.*** This is an exploratory study focusing primarily on safety, and there are no preliminary data regarding the effects of metformin in dengue on which to base a sample size calculation. A target sample size of 60 patients was chosen based on clinical judgement and feasibility considerations. Using the trend in VCAM over time, which is one of the secondary endpoints, by assuming a slope of change in concentration over time at 0.34 (log
_2_VCAM concentration per day, data based on biomarkers of endothelial function in dengue), we conducted a power calculation using a t-test to compare effects on endothelial function between two groups. It is suggested this study will have a power of 80% to detect a difference of at least 0.023 (log
_2_VCAM concentration per day) in the slope of change.

***Statistical analysis.*** The primary analysis population will include all patients from cohort 1 and cohort 2, plus 60 controls as mentioned previously. Baseline characteristics and outcomes will be summarised for each treatment group. The cohort of patients enrolled in this study will form the active treatment group, while the control group will consist of overweight and obese dengue patients that participated in a matched cohort observational study, none of whom received metformin therapy. Continuous variables will be described using medians and quartiles, while categorical variables will be described in terms of frequencies and percentages.

The primary endpoint (number of AEs), will be compared between the treatment groups using negative binomial regression model. The clinical, biomarker, immunological will be compared between the treatment arms using linear regression or random effects model for continuous endpoints, and Cox regression for time-to-event endpoints (fever clearance time, time to first undetectable viremia measurement, time to first negative NS1 measurement). All comparisons will be adjusted for age, sex, and day of illness, as patients will not be randomized. For percentage increase in HCT and area under the curve of viraemia, comparisons will be also adjusted for the pre-dose value of the respective marker.

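### Arm is set by 2-week enrolment block, but the fixed adjustment set has no season, calendar-time or block term, and the power calculation treats patients as independent

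*Protocol article*

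**What the plan says.** The section on screening, enrolment and retention states that the study is not randomised: "While not an RCT, this trial is designed to enroll patients contemporaneously with an observational obesity trial". To limit selection bias, the wards follow a time-block rule: "This involves only one study enrolling for a 2-week time block". Patients cannot move between the studies: "if a patient fails screening assessment or declines enrollment into one of the trials, they are not eligible for the other". Serotype shift is named as a threat and is met by design alone, through controls who are "enrolled on same wards, with the same standard of care during the same dengue season". The Design section, however, expects recruitment to run over two seasons.

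On group sizes: "The 60 patients receiving treatment will be compared to 60 overweight or obese patients with standard of care".

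The statistical analysis paragraph fixes the covariates: "All comparisons will be adjusted for age, sex, and day of illness, as patients will not be randomized". The only additions are the pre-dose values for haematocrit increase and viraemia area under the curve. The models are also named. For safety: "The primary endpoint (number of AEs), will be compared between the treatment groups using negative binomial regression model". For the other endpoints: "using linear regression or random effects model for continuous endpoints, and Cox regression for time-to-event endpoints". The sample size paragraph claims 80% power for a slope difference of 0.023 log2 VCAM per day, from a two-group t-test.

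**The concern.** Under the block rule and the ban on crossing over, a patient's admission date decides the arm, and everyone enrolled in a block belongs to the same arm. Allocation is therefore by block, while the named covariates describe only the patient. Day of illness counts from fever onset and carries no information about calendar time.

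Two things are at stake. The first is bias: a trend in serotype, case mix or ward practice that is not evenly spread over the two sets of blocks will appear as a treatment effect. The second is precision: if patients in one block resemble each other, a patient-level standard error overstates the information in 120 patients. Both bear on the safety comparison and on the secondary endpoints. The Discussion says that established safety, with improvement in any secondary endpoint, would warrant a larger randomised trial.

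This is more than a detail left to a later analysis plan. The covariate sentence is written as applying to all comparisons, so an analysis plan that followed it would carry the omission forward.

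**Working it through.** **Inputs from the protocol:** 60 per group; blocks of 2 weeks; two seasons; detectable slope difference 0.023; power 80%.

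**Assumed, because the protocol does not give them:** the number of blocks, the within-block correlation (ICC), the block order, the SD of the VCAM slopes, and a two-sided 5% test.

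**1. The protocol's own power figure.** It cannot be reproduced without the SD, only solved backwards. With 60 per group, SD = 0.023 / [√(2/60) × (1.960 + 0.842)] = 0.023 / 0.5115 ≈ 0.045. The 80% figure therefore rests on a standardised difference of about 0.51 and on independent patients.

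**2. Independent block-to-block variation, equal blocks.** With mean block size m = 120/blocks, the design effect is DE = 1 + (m − 1) × ICC. The true type I error of the patient-level test is 2 × [1 − Φ(1.96/√DE)].

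| ICC | DE, 26 blocks (m = 4.62) | Type I error | DE, 16 blocks (m = 7.5) | Type I error |
|---|---|---|---|---|
| 0.01 | 1.04 | 5.4% | 1.07 | 5.8% |
| 0.02 | 1.07 | 5.8% | 1.13 | 6.5% |
| 0.05 | 1.18 | 7.1% | 1.33 | 8.9% |
| 0.10 | 1.36 | 9.3% | 1.65 | 12.7% |

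Simulation of the patient-level t-test with 24 equal blocks agrees with the formula: 7.1% at ICC 0.05 and 10.0% at ICC 0.10.

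**3. Unequal blocks.** Simulation over the same 16 to 26 blocks gives about 6–8%, 9–12% and 13–17% at ICC 0.02, 0.05 and 0.10. The upper end needs marked imbalance. A rate of 17% corresponds to DE = (1.96/1.372)² = 2.04. Setting 1 + [(1 + CV²) × 7.5 − 1] × 0.10 = 2.04 gives 1 + CV² = 1.52, so the block sizes would have a coefficient of variation of about 0.72.

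**4. Power.** With 24 blocks (m = 5), ICC of 0.01, 0.05 and 0.10 gives DE of 1.04, 1.20 and 1.40. At 60/DE effective patients per group, the nominal 80% becomes 78%, 73% and 66%.

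**5. Slow drift.** Suppose the drift is linear over B blocks and accounts for a share ICC of the outcome variance. The SD of the block index is √[(B² − 1)/12], which is 6.92 for B = 24 and 3.45 for B = 12.
- *Strictly alternating:* the arms differ by one step on average, so the bias is √ICC / SD(index). For 24 blocks this is 0.224/6.92 = 0.03 SD at ICC 0.05 and 0.316/6.92 = 0.05 SD at ICC 0.10. Simulated type I error is 4.6% at both. Seasonal (sine) drift gives 3.9–4.4% and autocorrelated drift 4.9%.
- *Alternating, only 12 blocks:* the bias is 0.224/3.45 = 0.06 and 0.316/3.45 = 0.09 SD, with type I error of 6.1% and 6.7%.
- *One arm entirely first, 24 blocks:* the arms differ by 12 steps, so the bias is 12 × 0.224/6.92 = 0.39 and 12 × 0.316/6.92 = 0.55 SD. Type I error is 57% and 87%. This is an outer bound, not a description of the plan.

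**The case against.** A reader might infer that season or serotype drift is confounded with treatment as the trial stands. The documents do not support that. Controls are to be recruited contemporaneously, on the same wards and in a systematic way. If the 2-week blocks alternate, slow drift is nearly balanced, and step 5 shows patient-level errors about right or slightly conservative. The case with one arm entirely first runs against the stated intent. On the other hand, the protocol never says that the blocks alternate, so the balance is not guaranteed. The sequence could be disturbed, for example, if metformin enrolment paused for the committee's review of the first ten patients. Such a pause is an assumption; none is stated.

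A reader might also infer that the standard errors are certainly too small, or that every model assumes independent patients. Neither is established. The protocol gives no ICC and no block count, and at an ICC near 0.01 the effect is trivial. A random effects model is offered for continuous endpoints without naming its random unit. The unit is probably the patient, for repeated measures, but the text does not say. Variance estimation is also commonly left to an analysis plan, which is not shown here. What stands is the covariate list, which the protocol does fix, and the t-test behind the power statement.

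Finally, the study is exploratory, its sample size was set by judgement and feasibility, and it declares itself non-randomised. Randomising the block order would be a change of design, and this point does not need it. In an open-label study with one arm enrolling at a time, staff know which study is open under any order.

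**Conclusion.** The point holds in a conditional form. Arm follows the calendar block, recruitment is expected over two seasons, and the covariates fixed for all comparisons leave out season, calendar time and block. The power calculation ignores block as well.

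The bias depends on the unstated sequence. Under linear drift explaining 5–10% of the variance, it is about 0.03–0.05 SD with 24 strictly alternating blocks, and it rises when blocks are fewer or out of order. The understatement of error depends on block-to-block variation beyond slow drift. Over an assumed 16–26 blocks and ICC 0.02–0.10, type I error is about 6–13% with equal blocks and up to about 17% with markedly unequal ones. All these sizes rest on assumed block counts and ICCs, and the error rates are for a continuous outcome compared by a patient-level t-test. They were not computed for the negative binomial or Cox models.

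This should be changed: the remedy is cheap, and the protocol itself names the time-related threat.

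**What to change.** - Extend the covariate sentence so that every between-group model includes a season or calendar-time term.
- Use block-robust standard errors with a small-sample correction, or a block random intercept where it can be estimated, at least as a prespecified sensitivity analysis. With about 5 to 8 patients per block, the random intercept may be unstable in the negative binomial and Cox models, and the robust version is then the fallback.
- Name the random unit in the random effects model.
- State the block sequence and what happens to it if one study stops enrolling. Record each patient's block.
- State that the 60 controls come only from blocks interleaved with metformin blocks. This makes the promised contemporaneous recruitment explicit.
- Say that the 80% power figure assumes no block effect, or give it over a range of ICCs.

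The cost is a few lines of wording, one extra variable in the data set and slightly wider confidence intervals. Enrolment procedures need not change if the blocks already alternate.

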### Design

This is an open-label study investigating metformin therapy in 60 overweight and obese Vietnamese adults (30 patients) and children (30 patients). Age range of 10 to 30 years, who are admitted to the Hospital for Tropical Diseases (HTD) in Ho Chi Minh City (HCMC), Vietnam, with positive non-structural protein 1 (NS1) rapid test and onset of fever <72 hours prior to admission.

We will investigate the effects of five days of metformin treatment on the grounds that the critical phase of disease usually occurs around the fifth day of illness.

The trial will be conducted in two phases, with a dose escalation between phases (
Figure 1). In the initial phase (cohort 1), five young adults (age ≥16) and five children (age <16) with body mass index (BMI) >25 kg/m
^2^ (BMI-for-age >1 standard deviation – SD) will be provided with a low dose of metformin once daily at 850mg and 500mg, respectively. If the five-day safety and clinical data of cohort 1 show no safety concerns, the study will progress to the second phase (cohort 2). This will include 25 adults and 25 children, who will be given a weight-based dose of metformin; 1000mg (500mg twice daily) for participants with weight <60kg, and 1500mg (1000mg mane, 500mg nocte) for those ≥ 60kg. Of note, the actual number of patients in each cohort will depend on the results of safety reviews. Recruitment is expected to happen over two dengue seasons, and discharged patients will be asked to return for a single outpatient follow-up (FU) visit around day 28 of illness.

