### Primary endpoint

The primary endpoint of this study is an evaluation of the safety and tolerability of metformin therapy in overweight and obese young adults and children with dengue. The number of clinical and laboratory adverse events (AEs) occurring during the five study days (
Table 1), will be compared between the treatment population and the non-treated controls.

**Table 1. T1:** Adverse events.

1- Worsening level of consciousness (fall in GCS ≥ 2 points)
2- Change in blood pressure (PP < 20 mmHg, SBP < 90 mmHg or unmeasurable BP)
3- Vomiting (≥ 3 episodes separated by 15 minutes/ 24 hours)
4- Epigastric abdominal pain
5- Diarrhoea (≥ 5 episodes/24 hours)
6- Mucosal bleeding
7- Rash, urticaria
8- Increased lactate (≥ 3 mmol/L)
9- Episode of hypoglycaemia (glucose < 3.9 mmol/L or < 70 mg/dL)
10- Increased liver enzyme (AST or ALT > 400 U/L)
11- Acute kidney injury (eGFR reduction of >50% or < 30 ml/mn/1,73m ^2^ or plasma creatinine >2 fold increase from baseline)
12- Thrombocytopenia (Platelet < 20.000/uL)
13- Other event, specify: [________________________________________]

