### Safety reviews

The trial will be conducted in two phases, with a dose escalation if no safety concerns arise during the low dose stage. Metformin dosing will begin at 500mg (children) and 850mg (adults) once daily for 5 days in cohort 1. Daily patient safety reviews will be performed by study doctors using clinical and laboratory data to decide whether patients are safe to continue taking the study drug.

The study drug will be stopped if participants: (1) request withdrawal from the study; (2) develop any AEs, including severe renal impairment (GFR below 30mL/min/1.73m
^2^), elevated lactate to ≥ 3 mmol/L, severe liver involvement (AST/ALT > 400U/L), severe diarrhoea (≥ 5 episodes of loose stool/day), persistent vomiting (≥ 3 episodes/hour or ≥ 4 / 6hours) and hypoglycaemia (blood glucose < 3.9 mmol/l or < 70 mg/dL); (3) develop severe dengue (defined as admission to intensive care unit); or (4) are intolerant of metformin.

All AEs occurring during the trial/or until the FU visit at around day 28 of illness, will be recorded in the CRF, and whether or not attributed to trial medication. Specific AEs are shown in
Table 1. Laboratory events will be graded according to Common Terminology Criteria for Adverse Events (CTCAE) definitions. Clinical events will be assessed as mild, moderate, or severe. If the event is serious and not only related to the progression to severe dengue, or is fatal, then a serious AE form must be completed and the OUCRU CTU notified within 24 hours.

In cases of discontinuation due to AEs, participants will be followed up until the events have resolved or stabilised. A Data Monitoring Committee (DMC) review will take place after day 5 data is fully available for the first ten patients enrolled in cohort 1. Following satisfactory safety review of the tenth patient, metformin doses for all remaining patients (cohort 2) will be weight-based; 5 days of 1000mg (500mg twice daily) for those weighing <60kg and 5 days of 1500mg (1000mg mane, 500mg nocte) for those weighing ≥60kg. All AEs and serious adverse events (SAEs) will be recorded and reported to the Ethics Committees (ECs) for review. Further DMC meetings will take place 6 monthly to review enrolment, AEs, treatment received and FU information, and any other requested data.

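### The unlimited claim of blinded outcome assessment cannot cover the ascertainment of symptom and bedside adverse events in the open-label primary count

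*Protocol article*

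**What the plan says.** Screening, enrolment and retention lists measures against bias in a comparison that is not randomised. The last is that "independent study investigators will perform a blinded outcome assessment for all patients". The article does not say which outcomes the assessors review, what material they see or how it is masked.

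The Primary endpoint section compares treated patients with untreated controls on "The number of clinical and laboratory adverse events (AEs) occurring during the five study days". Statistical considerations analyses this count by negative binomial regression. Table 1 has 13 lines. Some are laboratory cut-offs; others have no threshold at all, such as "4- Epigastric abdominal pain", "6- Mucosal bleeding" and the open line "13- Other event, specify".

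The study is open-label (Design), with dosing directly observed on the wards (Treatment and drug dispensation). Controls come from a separate observational study, and the two studies enrol in alternating two-week blocks. On safety data, Safety reviews says "Daily patient safety reviews will be performed by study doctors using clinical and laboratory data", in order to decide whether the drug continues. Under Data collection, AE details go on specific forms, "together with an assessment as to whether the events are likely to have been related to any treatment received".

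**The concern.** A reader will take the blinding statement as covering the primary endpoint, because nothing is excluded from it. A symptom event enters the count only if the patient mentions it or someone asks, and if it is then written down. In an open-label study these steps happen with the treatment known. A masked reader who comes later can reclassify what is on the record but cannot restore what never reached it.

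The bias could go either way. Staff alert to gastrointestinal effects might note more symptoms on metformin; staff who regard the drug as well tolerated might note fewer. Calling something an AE also has a consequence in one arm only, since Safety reviews makes AEs a reason to stop the study drug. The Discussion makes a larger randomised trial depend partly on safety being established here, so the weight that the AE comparison can bear matters. The problem would remain even if both arms had identical visits and tests.

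**Working it through.** The protocol gives no figure that tests this point. The only power statement concerns the VCAM slope and has no bearing on it. The check is therefore a reading of the text, followed by an illustration of size.

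**Step 1. Sort Table 1 by what a masked assessor could do.**

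| Items | Content | Source | Masked derivation possible? |
|---|---|---|---|
| 2 | Blood pressure limits | Vital-sign record | Yes |
| 8–12 | Lactate, glucose, AST/ALT, kidney function, platelets | Laboratory and point-of-care record | Yes |
| 1, 3, 5 | Consciousness score, vomiting, diarrhoea | Threshold given, but depends on bedside observation or patient report | Classification only |
| 4, 6, 7, 13 | Epigastric pain, mucosal bleeding, rash/urticaria, other | No threshold; report and judgement | Classification only |

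This gives 1 + 5 = 6 lines that can be derived masked and 3 + 4 = 7 lines whose ascertainment is open-label. These are lines on a form, not shares of events.

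**Step 2. What masking would require.** Removing the treatment arm alone is not enough. Study identity, dosing and relatedness entries can point to the arm. So can calendar dates, because only one study enrols in any two-week block.

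**Step 3. Illustration of size (all inputs assumed).** Let a fraction s of control AEs be soft, let soft events be recorded with relative excess e on metformin, and let there be no true effect. The apparent rate ratio is RR = 1 + s × e.

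With 1.5 AEs per control, 0.5 of them soft (s = 1/3):
- 30% under-recording: (1.0 + 0.5 × 0.7)/1.5 = 0.90
- 50% over-recording: (1.0 + 0.5 × 1.5)/1.5 = 1.17
- 100% over-recording: (1.0 + 0.5 × 2)/1.5 = 1.33

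With s from 4/13 to 1/2, 50% over-recording gives 1.15 to 1.25, and 100% gives 1.31 to 1.50.

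**Step 4. Effect on a nominal two-sided 5% test.** Take 60 per arm, a control mean of 1 to 2 AEs, negative binomial dispersion k of 0.25 to 1.0 and s from 4/13 to 1/2. The variance is Var(log RR) = (1/μ₀ + k)/60 + (1/μ₁ + k)/60.

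Example: μ₀ = 1, k = 0.5, s = 1/2 and e = 0.5 give μ₁ = RR = 1.25. The variance is 1.5/60 + 1.3/60 = 0.0467, so the standard error is 0.216. Then log(1.25)/0.216 = 0.223/0.216 = 1.03, and the test rejects with probability 0.18 instead of 0.05.

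Over the whole grid, the false-positive rate is 6% to 12% for 25% over-recording, 9% to 31% for 50%, and 19% to 78% for 100%. Under-recording would bias towards apparent safety.

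**The case against.** The strongest reply is that the article is candid about its design: open-label, not a randomised trial, exploratory and a pilot. The masking procedure may be in the full protocol, which is not shown. Daily symptoms and signs also go into the case report form, so assessors need not be confined to entries already labelled as AEs and could classify from masked daily records. This stands as far as classification goes. No fuller procedure, however, can blind the elicitation of symptoms in an open-label study, so the unlimited wording still claims too much.

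Several stronger readings are tempting, but the document does not support them:

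- **That the protocol has doctors who know the arm find, record and grade the events.** Safety reviews gives study doctors the task of reviewing data to decide on continuing the drug. Neither there nor under Data collection does the article name who records or grades events. That arm-aware staff do so is an inference from the open-label design, although a strong one.
- **That the claimed protection does not exist.** Masked classification is feasible, and the thresholds in items 2 and 8 to 12 can be applied blind.
- **That the AE form by itself unmasks the assessor.** The relatedness question concerns any treatment received, and the field can be removed before review.
- **That subjective grading distorts the primary result.** The primary analysis counts events, and grade does not enter it.
- **That a bias of known size is present.** Every event rate and degree of mis-recording in the illustration is assumed.

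**Conclusion.** The concern holds in a limited form. The blinding statement is broader than the design can deliver. It can be true for classification and for events derived from charts and laboratory files. It cannot be true for the ascertainment of items 1, 3 to 7 and 13, which feed the primary count. The conclusion rests on the open-label design and on the inference that people aware of treatment elicit and record these events.

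No size can be established from the document. The rate ratio of 0.90 to 1.33 under no true effect shows only that moderate differences in recording could look like a modest harm or benefit. The sample size is unaffected. The change is worth making because it alters how the safety comparison may be described and how much it can support.

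**What to change.** 1. Limit the blinding statement to classification and to outcomes that can be assessed masked. Describe ascertainment of items 1, 3 to 7 and 13 as open-label.
2. State who records and who classifies AEs, and use the same AE elicitation and recording in the metformin study and the observational study.
3. Have the assessors already planned derive items 2 and 8 to 12 by one algorithm in both arms, from vital-sign and laboratory records. Remove the arm, study, dosing, causality and calendar-date fields first. Use scheduled measurements only, because Data collection allows more frequent tests when clinically indicated, and those depend on clinicians who are not blind.
4. Pre-specify a negative binomial comparison of these events as a supportive analysis beside the total count, and interpret the total in its light.

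The cost is protocol wording, a masked data extract and one more model. No new staff are needed. The downside is that the masked subset has fewer events and a wider interval, so it supports the total count and does not replace it.
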